### Interventions

Participants in the intervention group will receive four 500-mg capsules of myo-inositol, which is to be taken orally at 08:00 and 20:00 daily. This dose has been used in previous clinical trials in other patient groups and is well tolerated over 12 months, with no side effects reported [16–19, 45]. Furthermore, this dose has been reported to favourably modify lipid profile and reduce circulating concentrations of pro-inflammatory cytokines in other patient groups [16–19, 45], effects that would be expected to limit AAA growth [1, 8, 51]. Participants will be instructed to avoid ingesting aperients or coffee within 1 h of taking the study supplement because these may interfere with myo-inositol absorption [52]. Participants in the control group will receive four 500-mg capsules of inert cellulose powder, which is to be taken orally at 08:00 and 20:00 daily. It will be packaged in an identical fashion to the intervention drug by Pharmaceutical Packaging Professionals (Thebarton, Australia), an established current good manufacturing practice facility.

### Participant time line

The overall design of the IMAGEN trial is shown in Fig. 2. At vascular outpatient clinics, potential participants will be identified and pre-screened for suitability, and, if appropriate, informed consent will be obtained, after which they will be formally assessed against the eligibility criteria (Table 1). Individuals will undergo a medical examination, anthropometric assessment (height, weight, waist and hip circumference), resting blood pressure, heart rate and ankle-brachial index assessments, questionnaires (health-related quality of life and food frequency), a 24-h dietary recall survey, and collection of blood samples for measurement of full blood count (haemoglobin, red cell count, white cell count, platelets, neutrophils, lymphocytes, monocytes, eosinophils, basophils), urea and electrolytes (sodium, potassium, creatinine, estimated glomerular filtration rate, albumin, total bilirubin, urea, chloride, bicarbonate), liver function tests (alanine transaminase, aspartate aminotransferase, γ-glutamyl transpeptidase, lactate dehydrogenase), fasting lipids (cholesterol, triglyceride, HDL cholesterol and low-density lipoprotein [LDL] cholesterol), and fasting glucose. Serum, plasma and whole blood will also be collected for assessment of circulating proteins and genetic (DNA and RNA) analyses. Investigational blood samples will be collected into the following tubes: 2 x 5 ml SST, 2 x 4 ml ethylenediaminetetraacetic acid, 1 x 4 ml Sodium Citrate and 1 x 2.5 ml PAXgene (Qiagen, Valencia, CA, USA). Blood samples will be processed according to standard operating procedures and shipped to the study centre in Townsville. Baseline CT and ultrasound will be performed for detailed measurements of AAAs.

**Fig. 2 Fig2:**
[figure not shown]
Design of the Inositol in the MAnaGemENt of abdominal aortic aneurysm (IMAGEN) trial. *AAA* Abdominal aortic aneurysm, *CT* Computed tomography, *PWRI* Peak wall rupture index, *PWS* Peak wall stress

Eligible and consenting patients will be randomised to receive either 2 g of myo-inositol or identical placebo twice daily for 12 months. Participants will be contacted by telephone call at 1 month after commencing the trial medication and asked about adherence to the study drug regimen as well as adverse and clinical events. Phone consultations will be repeated at 3 and 9 months. Follow-up visits will occur at 6 and 12 months, when participants will receive ongoing questionnaires, clinical examinations, blood tests and imaging according to Fig. 1. The occurrence of adverse and clinical events and adherence to the study drug regimen will also be assessed. All participants, including those in whom medication is ceased, will be invited to follow-up visits for the duration of the study in the absence of AAA repair. Final follow-up will occur at 12 months after commencement of medication, at which point the participant will discontinue the prescribed medication and return any unused medication.

### Compliance

Previous studies suggest that compliance with dietary supplementation of 4 g of myo-inositol daily is excellent [19, 45]. To facilitate compliance, a number of techniques will be used, including providing participants with the telephone number of the local trial coordinator with instructions to contact in the event of possible supplement-related problems or consideration of discontinuation. In this event, arrangements will be made for the participant to be reviewed by the study physician to ascertain if discontinuation is required. The trial will also use a reminder system to facilitate compliance. This will consist of reminders from the local trial coordinator to each participant at 1, 3, 6 and 9 months after randomisation to check and encourage compliance. Participants will be provided with a compliance diary at the commencement of the trial. Participants will bring their diaries and remaining supplement capsules to review appointments at 6 and 12 months, and compliance will be checked by capsule and bottle counting. Where < 95% of capsules were taken since the last review, the study coordinator will attempt to work with the participant to identify the issues which have impacted compliance and provide suggestions on how to overcome these issues in future.

### Outcome assessment

Outcome assessment will be performed at baseline, 6 and 12 months. Participants will be imaged by ultrasound at baseline, 6 and 12 months and by aortic CT at baseline and 12 months. Blood will be collected at baseline, 6 and 12 months and will be used to assess biomarker outcomes and safety.

### Primary efficacy endpoint

The primary outcome measure will be AAA growth estimated by increase in total infrarenal aortic volume on the basis of CT. Previous studies indicate this is a reproducible and sensitive measure of AAA growth [53]. A standardised and established CT imaging protocol will be employed at all four centres, as previously described [53–55]. All CT images will be transferred to the central imaging centre in Townsville, where image quality will be confirmed. Total infrarenal aortic volume will be measured from the level directly below the renal arteries to the bifurcation using the Philips IntelliSpace Portal 7.0 (Philips Clinical Informatics, Amsterdam, The Netherlands), as previously described [53]. Central reading of the CT images will be performed by a single experienced observer who has previously been shown to have excellent imaging analysis reproducibility. The repeatability of central readings will be checked intermittently during the central reading period, which will span the duration of the trial.

### Secondary efficacy endpoints

Secondary outcome measures reflect the proposed mechanism of action of myo-inositol, are important and relevant clinical events, and are implicated in AAA growth.

#### Maximum AAA diameter assessed by CT

Maximum AAA diameter is the most validated marker of AAA rupture risk and currently the main determinant of when patients are selected for intervention [4–7, 56]. Maximum outer wall to outer wall AAA diameter will be assessed in anteroposterior (AP) and transverse orthogonal planes centrally from reconstructed aortic CT images obtained using a previously published reproducible protocol [53, 57–59]. The assessment will be performed by a single experienced observer who has previously been shown to have excellent imaging analysis reproducibility.

#### Maximum AAA diameter assessed by ultrasound

Participants will be assessed by ultrasound in the morning, having fasted from midnight. Maximum outer wall–to-outer wall diameter assessed in an AP orthogonal plane will be measured by experienced sonographers using a 3.75-MHz transducer and ultrasound machines present in the vascular laboratories of each centre (Toshiba Capasee, Toshiba Medical Systems, Duluth, GA, USA; Philips HDI 5000, Philips Medical Systems, Norcross, GA, USA; LOGIQ E9, GE Healthcare Life Sciences, Chicago, IL, USA), as previously described [44, 60]. The maximum AP inner wall-to-inner wall, leading edge wall-to-leading edge wall and outer wall-to-outer wall measurements on the largest AAA ultrasound image recorded at each time point will be centrally assessed by a single experienced observer who has previously been shown to have excellent imaging analysis reproducibility.

#### AAA PWS and PWRI

These parameters will be estimated by a single investigator using the A4research software (VASCOPS GmbH, Graz, Austria) with a reproducible and previously validated technique [2, 61, 62]. A 3D reconstruction of the AAA is produced from the CT images, and a fine element analysis mesh is automatically generated by the software. This is used to estimate the PWS and PWRI, providing a surrogate marker of rupture risk [61, 62].

#### Serum lipids

Total cholesterol, triglycerides, LDL cholesterol and HDL cholesterol concentrations will be assessed using automated assays (Hitachi 917; Roche Diagnostics GmbH, Mannheim, Germany) with serum obtained from patients who have fasted overnight. The inter-assay coefficient of variation (CV) for these assays has been shown to be between 2% and 5% in our previous studies [49, 50].

#### Circulating AAA biomarkers

The following biomarkers have been selected on the basis of their reported association with AAA and previous data suggesting they may be favourably modified by myo-inositol supplementation [16–19, 23–46, 63, 64]: serum resistin, plasma interferon γ, plasma CCL22, plasma D-dimer, plasma MMP-2, plasma MMP-9, plasma cathepsin S, serum OPN, plasma OPG and serum SOST. Concentrations will be measured using established commercial enzyme-linked immunosorbent assays (R&D Systems, Minneapolis, MN, USA) according to the manufacturer’s instructions and expressed as nanograms per millilitre. Intra-assay and inter-assay CV for all these assays are between 3% and 6% in our laboratory (concordance correlation coefficient ~ 0.999) [32, 35, 44, 47, 63–65].

#### Profiling of circulating RNAs

Blood will be collected into PAXgene tubes at baseline and at 6 and 12 months. RNA will be extracted from these samples and used to assess the expression profile of circulating cells. Established techniques will be used to assess expression profile, including microarrays, next-generation sequencing and RT-PCR as we have previously reported [66–68].

#### Health-related quality of life

Health-related quality of life will be assessed using the 36-item Short Form Health Survey (SF-36) completed at 0, 6 and 12 months and has previously been validated for use in patients with AAA [69]. Additional outcome measures include dietary analysis assessed by means of a food frequency questionnaire and 24-h recall interview at baseline and at 6 and 12 months, as previously described [70]. Finally, acute cardiovascular events, requirement for peripheral arterial intervention, AAA rupture, all-cause mortality, changes in background medication and withdrawal from the study dietary supplement (by indication) will be recorded. These data will be recorded through patient interview every 6 months, chart reviews and linked data, as previously described [71–73].

### Participant safety

Previous trials using dietary supplementation with 4 g of myo-inositol daily suggest it is associated with no ill effects. There have been no reports of excess gastrointestinal, cardiovascular, respiratory or cutaneous symptoms in those randomised to myo-inositol compared with placebo [16, 17, 19, 45]. Patient safety will be assessed at 6 and 12 months following randomisation by assessment of blood pressure and heart rate; laboratory parameters, including serum chemistry (liver function tests, glucose, creatinine, sodium, potassium, chloride, bicarbonate, calcium and phosphorous) and haematology (haemoglobin, differential white blood cell and platelet counts); and questions regarding adverse events (AEs). Participants will be contacted by telephone at 1, 3 and 9 months following randomisation to enquire about AEs. Furthermore, participants will be provided with full contact details of the site trial coordinators with instructions to contact them in the event of any AEs. All AEs will be reported via standardised forms to the coordinating centre and carefully monitored throughout the study. Serious adverse events (SAEs) will be defined according to current Australian GCP guidelines and will be reported according to the National Health and Medical Research Council (NHMRC) Safety Monitoring and Reporting in Clinical Trials Involving Therapeutic Goods guidelines (November 2016) [74–77]. All SAEs will be reviewed by the safety committee, which will consist of two independent vascular surgeons. The safety committee will concentrate on events which could be AAA-related, such as sudden death due to AAA rupture, or events that could be related to myo-inositol, such as gastrointestinal problems or electrolyte disturbances. Expected AAA rupture rates for small AAAs are ~ 1–2% per year [4–7]. Rupture rates > 5% per year will be considered cause for concern. In this instance, all other outcome data from the study will be analysed. AAA growth will be compared between groups using these data. The final decision to stop the study will take into account AAA ruptures, AAA growth data and any other serious complications. On the basis of findings, the safety committee will report their decision to the steering committee.

### Interim analysis

An interim analysis assessing trial efficacy will be conducted once approximately one-third of participants have completed 12 months of myo-inositol treatment. In this analysis, we will assess changes in AAA volume and diameter over time to determine whether (a) a suggested difference in AAA growth between participant groups is observed and (b) whether a priori calculated sample sizes will provide adequate power to detect any observed differences in AAA growth. These findings will be conducted by an independent statistician using dummy-coded data to separate patients into drug or placebo groups (e.g., X and Y), thereby maintaining trial blinding and minimising potential bias. In the instance of a clear difference in AAA growth rate between groups, the statistician will liaise with the dispensing pharmacist to determine if participants receiving inositol exhibit faster AAA growth than control participants. Findings from this interim analysis will be reported to members of the steering committee, who will consider concluding the trial if either (a) myo-inositol administration appears to be associated with accelerated AAA growth (ethical assessment) or (b) revised sample size calculations based on observed AAA growth for the cohort suggest that group sizes need to be increased beyond what can reasonably be achieved (futility assessment).

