### Randomisation

The randomisation scheme will be generated from Stata code (StataCorp, College Station, TX, USA) and maintained by the central clinical trial pharmacist. Randomisation to myo-inositol or placebo will be stratified by study centre, presence of diabetes and aortic diameter (30–34, 35–39, 40–44, 45–49 and ≥ 50 mm) as measured on ultrasounds. Randomisation will be blocked in a 1:1 ratio (randomly to a maximum block size of 8). The central and site trial managers will be blinded to treatment allocation. Eligible and consenting participants will be allocated to inositol or placebo groups via a telephone call. Once an allocation number is obtained, the trial supplement will be dispensed by the local clinical trial pharmacist (after randomisation and at the 6-month time point). Allocation concealment will be achieved by using a central randomisation centre and employing identical packaging of intervention and placebo. Participants, investigators and outcome assessors will be blinded to treatment allocation. In the case of an emergency where breaking of the group allocation blinding is required, the local study centre clinical trial pharmacist will be contacted.

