### Trial and data organisation

This project has been developed through collaboration between experts in the biology and clinical management of AAA, aortic imaging and clinical trials. The trial steering committee comprises senior vascular investigators from the centres involved and experts in drug trials and data analysis. This will be the main policy- and decision-making committee for the study and will meet by teleconference on a quarterly basis. The clinical trial randomisation centre will be located at the NHMRC Centre for Cardiovascular Research & Education in Therapeutics at Monash University. A study coordinator located at James Cook University will coordinate activities across all the participating sites, assisting with local ethics reports, and communicating with the local sites, including updates and maintenance of the trial website, central computerised randomisation, data collection, entry and processing. Trial coordination will be facilitated by a clinical trial network established by the National Health and Medical Research Council-funded Centre of Research Excellence for Peripheral Arterial Disease. To determine whether important differences in the incidence of significant AEs exist between the treatment arms, an independent safety committee has been formed. The core imaging/biomarker laboratory located in Townsville will receive DICOM images of the CT scans and frozen serum/plasma to assess the CT and biomarker outcomes. Baseline and follow-up data will be collected on CRFs. All data will be stored in a central database and examined for data quality. A publications committee will oversee the preparation of reports arising from the study.

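### The interim growth comparison goes to a steering committee that includes site investigators, so X/Y coding does not keep them blind to the comparative result

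*Protocol article*

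**What the plan says.** All references are to the protocol article.

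- **Interim analysis, timing and content.** The analysis takes place "once approximately one-third of participants have completed 12 months of myo-inositol treatment". It looks at volume and diameter and asks, among other things, whether "a suggested difference in AAA growth between participant groups is observed". Volume growth is the primary outcome.
- **Interim analysis, masking.** An independent statistician works "using dummy-coded data to separate patients into drug or placebo groups (e.g., X and Y), thereby maintaining trial blinding".
- **Interim analysis, decoding.** If growth clearly differs between the groups, "the statistician will liaise with the dispensing pharmacist to determine if participants receiving inositol exhibit faster AAA growth than control participants".
- **Interim analysis, recipient.** "Findings from this interim analysis will be reported to members of the steering committee". The committee may then conclude the trial on either of two grounds: growth appears accelerated on myo-inositol, or the revised sample size is out of reach.
- **Trial and data organisation.** "The trial steering committee comprises senior vascular investigators from the centres involved", together with experts in drug trials and data analysis. It is the main decision-making body.
- **Randomisation.** "Participants, investigators and outcome assessors will be blinded to treatment allocation".
- **Participant safety.** An independent safety committee of two vascular surgeons exists. The Interim analysis section gives it no role.

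**The concern.** The plan presents dummy coding as the safeguard for the blind. Coding of this kind masks the statistician until the labels are decoded. It does nothing for the people who receive the findings afterwards and must act on them by named arm. Some of those people are investigators at the four recruiting centres, a group the plan says is blinded.

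Investigators who believe that the supplement works, harms or is futile may change whom they approach, how hard they work to keep participants in the study and how they conduct follow-up. The plan relies on clinical judgement at several points: suitability for entry, likely compliance, expected need for repair, and review when a participant considers discontinuing. Follow-up visits are offered only in the absence of repair, so changes in conduct can also cost 12-month scans. Once site investigators have seen comparative results, this cannot be undone.

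**Working it through.** **1. Does the committee need the arm identity?** Set the steps in the Interim analysis section in order:

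- Growth is compared as X against Y.
- If the difference is clear, the statistician learns from the pharmacist which label is inositol.
- Findings go to the steering committee.
- The committee considers ending the trial if inositol appears to speed growth.

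The last step cannot be carried out on X and Y alone. Either the committee is told the direction by arm, or it cannot apply its own criterion. Even without explicit labels, a committee that sees a clear X/Y difference and hears no concern about inositol can infer that inositol looks better.

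**2. Who is on the committee?** Trial and data organisation places senior investigators from the participating centres on it. Randomisation says investigators are blinded to allocation. The Interim analysis section says blinding is maintained. Steps 1 and 2 together contradict the Interim analysis claim as regards the comparative result, and they are in tension with the Randomisation statement.

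**3. The plan's sample size, reproduced first.** The inputs come from Sample size and power calculations: means 8.1 and 4.9 cm³ (difference 3.2), SD 6.9 in both arms, α = 0.05, power 80%.

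- Normal approximation, two-sided: n = 2 × (1.96 + 0.84)² × 6.9² / 3.2² ≈ 73 per group.
- Two-sample t test: 74 per group (power 80.0%), as stated.
- Dropout: 148 / 0.90 = 164.4, stated as 164.

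The sample size is not in dispute.

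**4. How many participants are still open to influence?**

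- Completers at the interim: 164 / 3 = 54.7, about 55, or about 27 per arm at 1:1.
- Not yet completed: 164 − 55 = 109, or 109 / 164 = 66%.

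This is an upper bound. It mixes people not yet recruited with people already on supplement, and the recruitment pace is not given.

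**5. How reliable is the message they would receive?**

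- Standard error of the difference: 6.9 × √(2/27) = 1.88 cm³.
- 95% half-width: 1.96 × 1.88 = 3.7 cm³, wider than the 3.2 cm³ target itself.
- Power at two-sided 0.05 if the target effect is true: Φ(3.2/1.88 − 1.96) = Φ(−0.26) ≈ 40%.

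The findings could mislead those who see them in either direction.

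**The case against.** Several points on the other side are sound.

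- **Group level only.** The Randomisation section promises blinding to allocation, and nothing in the interim plan releases individual codes. A reader might infer that the double-blind is broken outright, or that investigators could recruit, retain or refer for repair differently by arm. The documents do not support this: someone who does not know a participant's allocation cannot act on it. The CT outcome is also read centrally, by an assessor stated to be blinded. The risk that remains is more diffuse and largely non-differential.
- **The rupture trigger.** Under Participant safety, a high rupture rate leads to a step in which "AAA growth will be compared between groups using these data". A reader might see a second leak here. The same section ends with the safety committee passing its decision to the steering committee, so it does not describe comparative data going to site investigators. It is close to the arrangement the interim analysis needs.
- **Mixed membership.** The committee also contains trial and data-analysis experts. That its site members personally enrol or review participants is plausible but not stated.
- **Conditional decoding.** Labels are decoded only if the difference is clear, a term left undefined. If it meant two-sided p < 0.05 (an assumption), this would happen about 40% of the time under the full effect and about 5% under none.
- **Content of the findings.** The article does not say word for word that decoded labels or effect sizes are tabled, and reporting format is often left to a charter.

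The last point is the strongest, but it does not remove the problem. The article itself fixes both the recipient and a criterion that depends on direction by arm, so a charter consistent with it would still have to convey that direction.

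**Conclusion.** The concern holds in a limited form. As written, the Interim analysis section lets investigators from the recruiting centres learn, at group level, how growth compares between inositol and placebo while the trial continues. This contradicts that section's claim to maintain blinding and sits badly with the blinding of investigators under Randomisation.

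Up to about 109 of 164 participants have not completed 12 months at that time, and the estimate disclosed has a standard error of about 1.9 cm³ against a 3.2 cm³ target. The exposure is to recruitment, retention and general conduct.

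The conclusion rests on three assumptions: that the findings convey the direction by arm, as the stopping criterion requires; that the interim falls at about one-third of 164; and that the planning SD of 6.9 cm³ applies. The documents do not allow the resulting bias to be quantified.

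**What to change.** Amend the Interim analysis section before the interim takes place:

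- Send all comparative output, and any decoding of X and Y, only to the independent statistician and the existing independent safety committee.
- Have that closed group apply the criterion on accelerated growth.
- Give the steering committee only a recommendation to continue or stop, as Participant safety already does for the rupture trigger.
- If the steering committee needs a figure for the sample-size check, give it the blinded pooled SD. Under the planned effect, ignoring arm inflates this only slightly: √(6.9² + 1.6²) = 7.1 cm³ against 6.9. Any check based on the observed difference should stay in the closed group, because a revised sample size computed from that difference can reveal its size.

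**Cost.** No sample-size figure changes. The safety committee's remit, now centred on serious adverse events, widens to an efficacy interim. The steering committee must act on a recommendation without seeing the comparative data. Moving the steering committee's check to a pooled SD also narrows the present second question, which concerns power for observed differences, so that is a small design change and not only a rewording.

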### Sample size and power calculations

It is hypothesized that dietary supplementation with 4 g of myo-inositol daily for 12 months will reduce AAA growth by 40%, as evidenced by limiting increase in AAA volume from 8.1 ± 6.9 cm^3^ to 4.9 ± 6.9 cm^3^. Estimated outcomes for the control group are based on CT volume measured in a pilot cohort [53]. An effect size of 40% is based on the consideration of outcomes likely to be required for clinical efficacy. For example, if myo-inositol reduced annual increase in AAA size by 40%, the estimated time for an AAA initially measuring 40 mm to reach the commonly employed intervention level of 50 mm would be increased from 5 to ~ 7 years. Given that the annual mortality rate due to non-AAA-related causes is ~ 5% in patients with small AAAs, this reduction in growth could be expected to result in ~ 10% less patients requiring interventions over 5 years. This has significant potential social and economic benefit, with a possible cost saving of ~ $1 million per year [5, 6, 12]. On the basis of these estimated outcomes, 74 participants per group are required (80% power, α = 0.05) to detect the hypothesized reductions in AAA volume. Using data from a pilot cohort, it is estimated that this sample size will have a power of ~ 85% to detect a 40% reduction in orthogonal AAA diameter increase, assuming that the SD for the intervention group reduces in line with the mean. Allowing for a dropout rate of 10%, a total of 164 patients will be required. Sample sizes were calculated using G*Power 3.1 software.

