### Data analysis

Analysis of primary and secondary endpoints will be based on intention to treat at the time of randomisation. All participants who meet the eligibility criteria, provide written informed consent and are enrolled in the study will be included in the primary analysis, regardless of adherence to supplement allocation. The efficiency of randomisation will be assessed by comparing the distribution of recognized determinants of AAA growth, such as initial AAA diameter, and background medication between the intervention and control groups.

The primary efficacy parameter is the between-group difference in mean AAA growth over 12 months as estimated by infrarenal aortic volume measured by CT. If there were to be no dropouts, the observed mean AAA volume increase over 12 months would be compared using a two-sample *t* test. However, it is expected that 10% of participants will drop out. AAA growth will therefore be analysed using a linear mixed model, specifying zero difference between treatment groups at baseline. The model will have two repeated dependent measurements. The fixed part of the model will contain the following covariates: time for CT measurement as a categorical variable, treatment, and interaction between treatment and CT time. The covariance part of the model will constitute a linear covariance matrix containing the following parameters: variance of CT measurements and covariance parameters. Without reference to the fixed part of the model, the goodness of fit of the assumed covariance model will be investigated. If necessary, the model will be extended with additional terms. The analysis will be performed using the PROC MIXED procedure in SAS software (SAS Institute, Cary, NC, USA), which is capable of fitting arbitrary linear covariance matrices. The main null hypothesis that will be tested is based on the treatment effect as estimated by this model at 12 months on CT measurements.

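### The interim futility criterion appears to re-power the trial on the difference observed in about 27 patients per arm; if followed, it would often flag a truly effective treatment as futile, and the stated 80% power makes no allowance for it.

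*Protocol article*

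**What the plan says.** The Interim analysis section of the protocol article plans one efficacy look when roughly a third of participants have completed 12 months. An independent statistician works with data split into two coded groups. One stated purpose is to determine "whether a priori calculated sample sizes will provide adequate power to detect any observed differences in AAA growth". The findings go to the steering committee, which will consider concluding the trial on either of two grounds: apparent acceleration of growth on myo-inositol, or futility. Futility arises if "revised sample size calculations based on observed AAA growth for the cohort suggest that group sizes need to be increased" beyond what is reasonably achievable. No achievable maximum is given.

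Sample size and power calculations plans for "limiting increase in AAA volume from 8.1 ± 6.9 cm^3^ to 4.9 ± 6.9 cm^3" and concludes that "74 participants per group are required (80% power, α = 0.05) to detect the hypothesized reductions in AAA volume". It adds: "Allowing for a dropout rate of 10%, a total of 164 patients will be required". The interim look is not mentioned there.

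**The concern.** The section describes the input to the re-estimation in two ways. The power question refers to observed differences in growth; the futility criterion refers to observed growth for the cohort. The first phrase, together with the split into coded groups, points to re-powering on the interim between-group difference.

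That is an unreliable basis for futility. The required sample size varies with one over the square of the observed difference, so ordinary noise in a third of the data can produce very large sizes. The rule would set aside the 40% reduction that the protocol justifies as the effect likely to be needed for clinical efficacy. It would also ignore what the remaining two-thirds of participants will contribute. At stake is an early stop, labelled futile, of a correctly sized trial of a treatment that works as hypothesised.

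**Working it through.** **Inputs from the protocol.** Mean volume increase 8.1 against 4.9 cm³, SD 6.9 in both groups, 80% power, α = 0.05, 74 per group, 10% dropout, total 164 (Sample size and power calculations). Allocation 1:1 (Randomisation). A two-sample t test as the reference comparison (Data analysis). A look at about one-third (Interim analysis).

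**Assumption.** The achievable maximum per arm is not in the document. I used 74, 111, 148, 222 and 370, which are 1, 1.5, 2, 3 and 5 times the planned 74.

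**1. The plan's own figure.** Difference 8.1 − 4.9 = 3.2 cm³; standardised 3.2/6.9 = 0.464. With two-sided α the normal approximation gives 2 × (1.960 + 0.842)² / 0.464² = 15.70/0.215 = 73 per group. The noncentral t calculation gives 74 (power 80.02%). One-sided α would give 58, so two-sided was used. Dropout: 148/0.9 = 164.4, against 164 stated. The sample size is sound.

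**2. Precision at the look.** 164/3 ≈ 55, or about 27 per arm. SE = 6.9 × √(2/27) = 1.88 cm³. With a true difference of 3.2, the 95% range of the interim estimate is 3.2 ± 1.96 × 1.88, about −0.5 to 6.9 cm³.

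**3. Chance of a futility signal with the planned effect true.** Required n per arm = 15.70 × 6.9² / (observed difference)². This exceeds a ceiling C when the observed difference is below 6.9 × √(15.70/C). For C = 148 the threshold is 2.25 cm³, and Φ((2.25 − 3.2)/1.88) ≈ 0.31. A difference of zero or less also counts as a signal.

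**4. Overall power if the signal is followed.** Simulation of 400,000 trials with the interim SD estimated; without a look, power is about 80%.

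| Assumed ceiling per arm | Threshold (cm³) | Futility signal | Power, continuing at 74 | Power, enlarging up to ceiling |
|---|---|---|---|---|
| 74 | 3.18 | 49% | 48% | 48% |
| 111 | 2.59 | 37% | 57% | 58% |
| 148 | 2.25 | 31% | 63% | 65% |
| 222 | 1.83 | 23% | 68% | 72% |
| 370 | 1.42 | 17% | 72% | 78% |

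Taking one-third of the 148 evaluable participants instead (about 25 per arm) moves these figures by about one point.

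**5. Other readings of the criterion, planned effect true.**

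- Updating only the SD and keeping 3.2 cm³: the revised size exceeds 111 in about 1% of trials and 148 in about 0%. It exceeds 74 itself in about 45%, so this reading is harmless only if some increase is achievable.
- Keeping the 40% reduction but applying it to the observed control mean: about 13% at 111, 4% at 148 and 0.6% at 222.

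**6. A conditional-power rule at the same look.** Information fraction t = 27/74 = 0.365. Planned drift θ = 3.2/(6.9 × √(2/74)) = 2.82. Conditional power at the planned effect is below 20% when the interim z is below (1.96 − 0.842 × √0.635 − 0.635 × 2.82)/√0.365 = −0.83, an observed difference of about −1.56 cm³. With the planned effect true, the mean interim z is 2.82 × √0.365 = 1.70, so the stop probability is Φ(−0.83 − 1.70) ≈ 0.6%, and power stays at about 80%. With no effect it is Φ(−0.83) ≈ 20%. Under the rule in step 3 the no-effect figure runs from about 95% (ceiling 74) to 77% (ceiling 370).

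**The case against.** **The criterion may not mean the observed difference.** The futility sentence speaks of growth for the cohort, which could mean the pooled SD, or growth with the 40% reduction kept. This stands as a real ambiguity: step 5 shows much smaller error rates once some increase is achievable. It does not remove the point, because the power question in the same section names observed differences and the data are split by group.

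**The rule is advisory.** The committee will only consider concluding. This stands. A reader might infer that the 80% power is simply not delivered; the document does not support that, because the loss arises only so far as the committee acts on the signal.

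**The ceiling is assumed.** This stands, so the loss is a range. Its direction does not depend on the ceiling: power was below 80% at every value examined.

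**Volume is not the only input.** The look also covers diameter, which is not modelled here. The figures describe the primary outcome alone.

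**Type I error.** A reader might infer that re-powering on the observed difference inflates false positives. The section sets out no procedure for enlarging the trial, and with the futility stop followed, two-sided type I error is below 5% (about 1.5–2.0% at ceilings of 148–370). Inflation would need enlargement without any futility stop.

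**Thresholds may be left to the full protocol or analysis plan.** Fair for the ceiling and the cut-off. The point concerns the basis for re-estimation, which the article does state.

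**Conclusion.** The concern holds in conditional form. The section ties futility to observed growth at one-third of the data and is inconsistent on whether that means the between-group difference. On the reading its wording better supports, with the planned effect exactly true, about 17–49% of trials would be flagged futile over ceilings of five times to one times the plan. If the flag is followed, power is about 48–72% without enlargement and 48–78% with it, and the stated 80% does not account for the look.

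This rests on three conditions: that the observed difference is the input, that the committee acts on the signal, and that the ceiling lies in the assumed range. The sample size itself is correct. Should fix, with moderate confidence.

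**What to change.** Reword the futility part of the Interim analysis section:

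- Re-check sample size only from the blinded pooled SD of growth, with the planned 3.2 cm³ kept, and say that size will not be changed on the observed difference.
- Assess futility as non-binding guidance to the steering committee, by conditional power at the planned effect. A cut-off of 20% is an example; the threshold is for the trialists to choose.
- If only the SD was meant all along, say so and remove the reference to observed differences from the power question.

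The harm look stays as it is. The data and the independent statistician are the same, so the direct cost is rewording. The real cost is fewer early stops when the treatment does nothing: about 20% with the example cut-off, against about 77–95% under the present rule on the observed-difference reading. That cut-off is reached only when the observed difference favours placebo by about 1.56 cm³, so trialists who want more early stopping may prefer a higher one and should report the power it gives up.
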